### Study population

Women with overweight or obesity (BMI: 26– 39.9 kg/m^2^) and with food addiction will be recruited from nutrition clinic of Shahid Beheshti University of Medical Sciences (SBMU) through advertisement and face-to-face communication. The diagnosis of food addiction will be based on the YALE Food Addiction Scale [29]. Women with overweight or obesity that obtain the necessary score will be enrolled in the study. Subjects who meet the inclusion criteria will be completely informed about the protocol of the study. Each participant will sign the informed consent form.

### Inclusion and exclusion criteria

For the present study, 60 adult women with the following inclusion criteria will be included: aged 20–65 years; BMI: 26–39.9 kg/m^2^; willingness to participate in the study; confirmation of food addiction after obtaining the necessary score (at least 1 clinical score+ at least having 3 out of 7 criteria) from the YALE food addiction questionnaire; not having any diseases such as cancer, diabetes, newly hypothyroidism, renal or liver failure; non-pregnant or lactating; not perimenopause (women with irregular menstruation due to menopause or less than 2 years after amenorrhea); not participating in a weight loss diet during the last 2 months; and were not smokers.

Patients will be excluded if taking any antibiotics in the last 1 month or during the study; taking any medication affecting study outcomes regularly; using probiotic products (probiotic supplements, yogurt, cheese, cakes, biscuits, and probiotic pasta) continuously (more than once a week) in the last month or during the study; using weight-loss or appetite-suppressing medications; drinking alcohol at any levels before or during the study; and women with irregular menstruations. Also, we will exclude participants who refuse to continue the study, need antibiotics or have difficulties in fasting for 14 h a day in the intervention group.

### Randomization, sequence generation, and concealment

Participants will be randomly allocated into two groups: the group receiving a low-calorie diet with the time-restricted feeding protocol or the control group receiving a low-calorie diet and will be followed up for 8 weeks. Stratified blocked randomization method is used to randomly assign people to two groups. The sequencing will be generated by one of the authors (AS) who is not going to assign participants into the study, so, allocation concealment will be ensured, as the author will not release the randomization code until the patient has been recruited into the trial by other authors (HI and [name]), which takes place after all baseline measurements have been completed. Participants are classified into overweight (26–29.9 kg/m^2^), grade 1 (30–34.9 kg/m^2^), and grade 2 obesity (35–39.9 kg/m^2^) based on BMI and randomly assigned to one of the control or TRF groups. Separate randomization is performed within each group for each BMI class. The size of the blocks is 4, two allocations are given to TRF group (A) and two allocations to Control Group (B). Six different permutations of AABB, ABAB, BBAA, BABA, ABBA, and BAAB will be created.

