### Sample size

The number of participants was calculated based on the changes in body weight, as a primary outcome. The number of participants in this study was determined by the difference in weight loss between the TRF and control groups of 2.3 kg [28]. This difference has a probability of 95% (*α*=0.05) and a power of 80% (*β*=20%), which is statistically significant. Using this method, each group was estimated to have 26 participants, so that after taking into consideration 20% attrition, every group will be comprised of 30 participants. Collectively, 60 women with overweight or obesity and food addiction will be enrolled.

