### Implementation

Potential participants will be invited to the study by HI and [name]. The sequencing will be generated by AS, who is not going to assign participants into the study.

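### One fixed block size of 4, known to the recruiters, leaves up to a third of allocations predictable if earlier assignments become known, so the claim of ensured concealment is too strong

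*Protocol article*

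**What the plan says.** The section on randomization, sequence generation and concealment describes stratified blocked allocation to a low-calorie diet with or without time-restricted feeding (TRF). The strata are three BMI classes (26–29.9, 30–34.9 and 35–39.9 kg/m²): "Separate randomization is performed within each group for each BMI class". There is one block size, "The size of the blocks is 4, two allocations are given to TRF group (A) and two allocations to Control Group (B", and the possible blocks are listed: "Six different permutations of AABB, ABAB, BBAA, BABA, ABBA, and BAAB will be created".

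On concealment, the list is generated by an author "who is not going to assign participants into the study" (Implementation section), and "the author will not release the randomization code until the patient has been recruited into the trial by other authors", which happens once baseline measurements are complete. From this the protocol concludes that "allocation concealment will be ensured".

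Other sections bear on the point:

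- Sample size: "Collectively, 60 women with overweight or obesity and food addiction will be enrolled".
- Study design: one nutrition clinic. The trial is labelled double-blind, without saying who is blinded.
- Study population: recruitment is partly face to face.
- Intervention: the TRF group eats between 10 am and 8 pm; controls fast for less than 12 hours.
- Adherence: twice-weekly calls compare a 24-hour recall with the participant's diet. The callers are not named.
- Inclusion and exclusion criteria: difficulty with the 14-hour fast is a reason for exclusion in the intervention group only.
- Trial status: recruitment runs from November 2021 to December 2023; the protocol version is dated 5/18/22.

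**The concern.** Concealment has two parts. The next code must be hidden, and it must not be deducible from the codes already issued. The protocol deals with the first and infers that the whole is secured. With one small fixed block size, the second part fails for anyone who knows the size and keeps a tally of assignments within a BMI class: the last place in each block is always determined, and the last two are determined after two identical assignments.

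The recruiters are described as authors, so the block size was never hidden from them. BMI class is known before randomisation, so a recruiter knows which tally applies. The arms differ in daily eating hours, so earlier assignments could easily become known in a single clinic with 60 participants. The document describes no step that keeps them from the recruiters.

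At stake is selection at entry. A recruiter who foresees the arm can hasten or delay a woman thought more or less able to cope with fasting. Adjustment can deal with imbalance in measured baseline factors, but not with selection on unmeasured ones such as motivation.

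**Working it through.** **Inputs.** Block size 4, ratio 2:2, six permutations and three strata (randomization section); 60 women (Sample size section).

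**The protocol's own figure.** The number of distinct 2:2 blocks is C(4,2) = 6, which matches the six sequences listed. The list is complete.

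**Allocations known with certainty.** An allocation is certain when one arm has already used both its places in the block. With the six blocks equally likely:

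- places 1 and 2: never certain
- place 3: certain in AABB and BBAA, so 2/6 = 1/3
- place 4: always certain

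The expected number per complete block is 1/3 + 1 = 4/3. The proportion is (4/3)/4 = 8/24 = 33.3%.

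**For 60 women in three strata.** A stratum of n women contributes 4/3 for each complete block. An unfinished block adds 1/3 if it holds three women and 0 if it holds one or two.

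- 20/20/20: 15 blocks × 4/3 = 20.0 (33.3%)
- 30/20/10: 28/3 + 20/3 + 8/3 = 18.7 (31.1%)
- 31/18/11: (28/3 + 1/3) + 16/3 + (8/3 + 1/3) = 18.0 (30.0%)

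Over every possible split of 60 into three strata, the range is 18.0 to 20.0, with an unweighted average of 31.2%. The document does not give the expected split. These are expected counts; the realised count depends on which permutations are drawn.

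**Best-guess accuracy.** The strategy is to guess the arm with more places left in the block and toss a coin when they are equal. The chances of being right at places 1 to 4 are:

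- place 1: 1/2
- place 2: 2/3
- place 3: 1/3 × 1 + 2/3 × 1/2 = 2/3
- place 4: 1

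The mean is (1/2 + 2/3 + 2/3 + 1)/4 = 17/24 = 70.8%.

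**Effect of changing the blocks.** Fixed sizes are enumerated exactly. Mixed sizes are simulated: 4,000 lists of 20 women per stratum, each size equally likely, and a guesser who knows the set of sizes and all earlier assignments in the stratum but not the order of the sizes.

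| Blocks | Certain in advance | Best guess correct |
|---|---|---|
| Fixed 4 | 33.3% | 70.8% |
| Fixed 6 | 25.0% | 68.3% |
| Random 4 and 6 | about 6% | about 69% |
| Random 2, 4 and 6 | about 4% | about 70% |

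Run on fixed blocks of 4, the same simulation gives 33.4% and 70.8%, in agreement with the enumeration. Varying the sizes removes most of the certainty. It hardly changes guessing, because the guesser mainly needs the running imbalance. Without knowledge of earlier assignments, every guess is right 50% of the time.

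**The case against.** The strongest objection is that everything depends on the recruiters learning earlier assignments, and the document does not say that they do. It gives them the task of inviting participants. It does not say who issues the diets or who makes the calls. This stands: a reader might infer that recruiters will know a third of the allocations, but the text supports only that they could.

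A reader might also infer that the trial cannot be masked at all. The document does not support that. It claims double blinding, and laboratory staff or outcome assessors could be blinded even though participants know their eating hours. What matters here is what the recruiters learn, and on that the document is silent.

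The safeguards are real. The list holder is separate from the recruiters, each code follows recruitment and baseline measurement, and eligibility is largely rule-based. The current code is therefore concealed in the ordinary sense; what remains is the narrower problem of prediction. A recruiter would have to follow three interleaved sequences and have a suitable woman in the right class at the right moment, although with 60 women this is not hard.

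Finally, blocks of 4 are a common choice and protect balance in strata that average 20 women. That is a good reason for small blocks, but not for a single size that the recruiters know.

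**Conclusion.** The point holds as a conditional risk. The protocol's argument for concealment does not follow, because withholding the current code does not prevent prediction from past ones. If recruiters know the block size (supported by their authorship) and the earlier assignments in each BMI class (likely, but not stated), they could be certain of an expected 18 to 20 of 60 allocations, or 30% to 33%. Twenty is the upper end and applies only when every block is completed.

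Two stronger conclusions are not supported. Nothing in the document shows that selection took place, and no size of bias in weight or any other outcome can be derived from it. Nor should the 71% best-guess accuracy be set against 50% as though varying the blocks would close that gap: it would remain at about 69% to 70%. The case for change is the near-removal of certain knowledge at little cost.

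**What to change.** For women still to be randomised:

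1. Have the existing sequence holder regenerate the remaining list within each BMI class with randomly varying block sizes, for example 4 and 6. State how a block that is open at the changeover will be handled.
2. Keep the sizes and their order from the recruiters.
3. Where possible, keep the running allocation list from the recruiters too. This is the step that would lower best-guess accuracy.
4. Replace the claim that concealment is ensured with a statement of what is concealed, from whom, and whether recruiters can learn earlier assignments.

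The cost is one new list and an amendment under the protocol's own amendment procedure. The downsides are slightly larger possible imbalance within a stratum and no effect on women already randomised.

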### Implementation

Potential participants will be invited to the study by HI and [name]. The sequencing will be generated by AS, who is not going to assign participants into the study.

### Intervention

In this study, patients receive the relevant diets for 8 weeks based on the group they are placed in. In both groups, after calculating the amount of calories required by each individual using the Mifflin formula [30] as much as 300–500 kcal will be deducted from the total energy required for each person (a 500 kcal reduction from calories is using for most of the cases, except for whom the calorie falls below 1200 kcal/d with 500 kcal reduction. In these cases, 300–400 kcal reduction will be used.) and accordingly, the low-calorie diet plan is given to each individual. The diet in each group will consist of 50–55% carbohydrates, 15–20% protein, and 30% fat. Patients in the TRF group will receive their meals from 10 h a day from 10 am to 8 pm [31] while the control group will have less than 12 h fasting.

### Adherence

In order to control the participants in terms of adherence to the regimen and prevent the loss of samples, they will be followed up twice a week by phone call. At every phone call we will make sure if the cases are still in the study and they do not have exclusion criteria (any need for antibiotic consumption, consuming probiotics, and…). Also, a 24-h recall of the last day is obtaining from individuals and it is compared to their diet to make sure if they are adhering to the diet. The data of the patients with more than 90% compliance with the intervention will be analyzed.

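### The only stated analysis set is women with more than 90% compliance, and one removal ground exists only in the TRF arm, so the comparison analysed is not the randomised one and can be biased

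*Protocol article*

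**What the plan says.** Three parts of the protocol article decide who enters the comparison.

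- **Adherence.** "The data of the patients with more than 90% compliance with the intervention will be analyzed". Compliance is judged during follow-up, from a 24-h recall taken at twice-weekly phone calls: "it is compared to their diet to make sure if they are adhering to the diet". The section does not say how the 90% is computed or whether eating times count.
- **Inclusion and exclusion criteria.** Besides the entry criteria, the section removes women during the study: "we will exclude participants who refuse to continue the study, need antibiotics", or those who "have difficulties in fasting for 14 h a day in the intervention group". Using antibiotics or probiotics, or drinking alcohol, during the study is also a ground for exclusion in either arm.
- **Intervention.** Under the control regimen, "the control group will have less than 12 h fasting".

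On allocation, "Stratified blocked randomization method is used to randomly assign people to two groups", and this happens after baseline measurements are complete. The Statistical analysis section lists the tests but names no analysis population, so the Adherence sentence is the only rule on the subject.

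**The concern.** Randomisation makes the two groups comparable as allocated. It does not make compliers in one arm comparable with compliers in the other. Women who keep closely to a diet may well lose more weight on any diet, so if the arms are filtered to different degrees, the retained groups can differ even when TRF adds nothing.

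The removal ground for difficulty with fasting makes unequal filtering a real prospect. It can be seen only once a woman has begun the assigned fast, and it names only the intervention group. The rule reaches every efficacy comparison, including the primary outcomes of weight and food addiction score. If week-8 outcomes are not collected from women who stop or break the diet, no later analysis can recover them.

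**Working it through.** **Step 1: timing and symmetry of each filter.**

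| Filter | When observed | Arms it can affect |
|---|---|---|
| More than 90% compliance | After randomisation | Both; whether it is equally hard to meet is not stated |
| Difficulty with the 14 h fast | After randomisation | TRF only (controls fast less than 12 h) |
| Refusal to continue; antibiotics, probiotics or alcohol during the study | After randomisation | Both |

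All three act after allocation, and one acts in a single arm. This settles the qualitative point without arithmetic.

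**Step 2: a scale for the size.** The Sample size section gives a 2.3 kg difference, α = 0.05, 80% power and 26 per arm, but no SD, so 26 cannot be verified independently. Solving backwards (two-sided):

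- Normal approximation: SD = 2.3 × √(26/2) / (1.960 + 0.842) = 2.96 kg.
- t-based: 26 per arm with 80% power needs a standardised difference of 0.792, so SD = 2.3 / 0.792 = 2.90 kg.

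I use 2.9 kg. The bias below is proportional to the SD, so 2.96 kg changes it by about 2%.

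**Step 3: bias with no true effect.** Assume that weight loss and a latent adherence score are bivariate normal with correlation ρ, and that each arm keeps its most adherent fraction p. The mean adherence score of those kept is λ(p) = φ(z) / p, where z = Φ⁻¹(1 − p):

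- λ(0.8) = 0.280 / 0.8 = 0.350
- λ(0.6) = 0.386 / 0.6 = 0.644
- λ(0.5) = 0.399 / 0.5 = 0.798

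Spurious difference in favour of TRF = SD × ρ × [λ(p in TRF) − λ(p in control)]. The retention rates and ρ are assumptions; the documents give neither. Type I error is from simulated trials with 30 per arm and a t test on the retained women.

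| Retained TRF / control | ρ | Bias | Share of 2.3 kg | Type I error |
|---|---|---|---|---|
| 60% / 80% | 0.5 | 2.9 × 0.5 × (0.644 − 0.350) = +0.43 kg | 19% | about 7% |
| 50% / 80% | 0.7 | 2.9 × 0.7 × (0.798 − 0.350) = +0.91 kg | about 40% | about 18% |
| 80% / 60% | 0.5 | 2.9 × 0.5 × (0.350 − 0.644) = −0.43 kg | −19% | about 8% |
| 80% / 80% | 0.5 | 0 | 0 | about 5% |
| 60% / 80% | 0 | 0 | 0 | about 5% |

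Milder assumptions give less: at 60% / 80% with ρ = 0.3 the bias is 2.9 × 0.3 × (0.644 − 0.350) = +0.26 kg, with a type I error of about 6%.

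**The case against.** The strongest general defence is that an unseen analysis plan may define an intention-to-treat set, or that the sentence only describes a per-protocol analysis. Neither stands. The sentence is a positive rule about which data are analysed. It carries no per-protocol label and has no companion analysis, and an analysis plan that said otherwise would contradict it.

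Several other objections do stand, and they limit what can be claimed.

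- **Direction.** A reader might infer that the result is biased toward TRF. The documents give no retention by arm and no link between adherence and outcome, and the sign reverses if more controls fail the filter.
- **Asymmetry of the 90% rule.** A reader might infer that TRF women must keep a diet and a time window while controls keep only a diet. Controls also have a timing rule, and compliance is described as a comparison of the recall with the diet. The only asymmetry the text establishes is the fasting-difficulty ground.
- **Numbers and power.** A reader might infer that the filter takes the analysed number below 26 per arm. With 30 enrolled, more than 4 women per arm would have to fail, and no compliance rate is given. The removals may also be meant to fall within the allowance made "after taking into consideration 20% attrition". That 30 × 0.8 = 24 is below 26 is a separate sample-size point. A power of about 70% for 18 against 24 women applies only if there is no selection. Under the 60% / 80%, ρ = 0.5 scenario itself, a true 2.3 kg effect is declared significant in about 88% of runs, because the bias adds to it.
- **Antibiotics and probiotics.** These removals apply to both arms and have a rationale for the microbiome-linked LBP and BDNF outcomes. They are a lesser problem than the TRF-only ground.

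**Conclusion.** The point holds and should be corrected before analysis. As written, the plan compares subsets selected after randomisation, with one selection ground present in only one arm, and offers no analysis of all randomised women. The comparison can therefore be biased. Toward TRF is the plausible direction, but the text does not support stating it as fact.

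Under the assumed values with lower TRF retention, the spurious difference runs from +0.26 to +0.91 kg against a 2.3 kg target, with a type I error of about 6% to 18%. It is −0.43 kg if the 60% and 80% rates are swapped between the arms, and about zero with equal retention or no correlation. These figures rest on the back-solved SD, a bivariate-normal model, and retention rates and correlations that the documents do not give. They illustrate the exposure and do not forecast the result. A loss of power below the planned 80% cannot be attributed to this rule from the documents.

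**What to change.** Replace the analysis sentence in the Adherence section with wording such as: *The primary analysis includes all randomised women in the arm to which they were assigned, whatever their compliance. Week-8 measurements are sought from every woman, including those who stop or break the diet.* Keep the set with more than 90% compliance as a labelled sensitivity analysis, and state how the percentage is computed and whether eating times count.

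In Inclusion and exclusion criteria, separate exclusions that apply before randomisation from events after it. State that the latter, including "need antibiotics or have difficulties in fasting for 14 h a day in the intervention group", do not remove a woman from outcome follow-up or from the primary analysis. This concerns data collection and analysis only; whether a woman continues the assigned regimen is a clinical matter outside this point. A supportive analysis without antibiotic or probiotic users may be kept for LBP and BDNF.

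The cost is a change of wording and a week-8 visit for women who stop the diet. The estimated effect may be smaller because non-adherers are included. The article describes the trial as still enrolling, so on that footing the follow-up could still be arranged.

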### Study outcomes

Primary outcomes of this clinical trial are the changes in anthropometric indices (including weight, BMI, hip circumference, waist-to-hip ratio, fat mass, muscle mass) and food addiction score. Secondary outcomes are changes in stress level, eating behavior, and serum levels of BDNF and LBP.

After obtaining the informed consent, the general profile sheet will be completed for each patient. Also, at the beginning of the study, the weight of each patient with light clothing and with the accuracy of 100 g and the height of each patient in a shoeless state will be measured by the meter mounted on the wall with an accuracy of 0.5 cm. Then, BMI of patients will be calculated and waist and hip circumferences are measured using meters with 0.5 cm accuracy. Also, the waist-to-hip ratio will be calculated. Then, body fat mass and muscle mass are measured by bioelectrical impedance analysis. The participants’ daily physical activity levels will be measured using the Standard Physical Activity Questionnaire (MET). The validity of this questionnaire has been confirmed [32]. Stress levels of subjects at the beginning and end of the study will be assessed using the Perceived Stress Questionnaire (PSS-14) [33]. The scoring method is that based on the 5-degree spectrum, a score of 0–4 is awarded to each item (never score 0 and most of the time score 4). Phrases 4-5-6-7-10 and 13 are scored inversely (never score 4 to most of the time score 0). Then, by collecting the items, the overall score is 0-56, which the higher score indicates more perceived stress [33]. Eating behavior will be measured using a three-factor eating questionnaire at the beginning and the end of the study. The questionnaire consists of 18 questions in 3 sections about cognitive factors related to eating, hunger, and emotional eating. The questionnaire is scored by questions 1 to 13 on a four-point Likert scale from one (definitely incorrect) to four (definitely correct). Questions 14 to 17 also have a separate Likert scale, and question 18 has an 8-degree Likert scoring scale. The higher rating in the cognitive factors associated with eating indicates a greater limitation in receiving calories to control body weight. Also, a higher hunger score indicates a person’s greater susceptibility to eating in response to hunger and a higher emotional eating score indicates a person’s greater susceptibility to excessive eating. The validity of this questionnaire has been measured in Iran [34].

In order to measure blood biochemical parameters, 5 cc of venous blood samples will be taken from the site of the bracing vein and after 12 to 14 h fasting by the laboratory technician at the beginning and the end of the study. Blood samples taken in tubes containing sodium citrate anticoagulants will be collected and centrifuged in the laboratory of the Shahid Beheshti Nutrition Faculty for 15 minutes at a speed of 500 rounds per minute and serums will be stored at − 80°C until the tests are performed. Serum levels of BDNF and LBP will be measured by the ELISA method with a human BDNF kit (PadginTeb, under the license of Zelbio, Iran) and a human LBP kit (PadginTeb, under the license of Zelbio, Iran) with the intra-assay and inter-assay CV of < 10% and <12%, respectively, for both kits in the laboratory of the Nutrition Institute of Shahid Beheshti University of Medical Sciences.

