### Objectives and hypothesis

Primary aims of this clinical trial are the changes in anthropometric indices (including weight, BMI, hip circumference, waist-to-hip ratio, fat mass, muscle mass) and food addiction score. Secondary aims are changes in stress level, eating behavior, and serum levels of BDNF and LBP. A TRF is expected to improve these aforementioned indicators.

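### Seven outcomes are labelled primary without ranking or a success rule, while the trial is sized on body weight alone

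*Protocol article*

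**What the plan says.** Two sections of the protocol article set the primary outcomes. Objectives and hypothesis states: "Primary aims of this clinical trial are the changes in anthropometric indices", then gives the list together with the food addiction score, and adds: "A TRF is expected to improve these aforementioned indicators". Study outcomes repeats the list: "including weight, BMI, hip circumference, waist-to-hip ratio, fat mass, muscle mass) and food addiction score". Neither section orders the outcomes or says how many must improve for the trial to succeed.

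The Sample size section uses one of them: "The number of participants was calculated based on the changes in body weight, as a primary outcome". The target is "the difference in weight loss between the TRF and control groups of 2.3 kg", with alpha 0.05 and power 80%, and "each group was estimated to have 26 participants" before an allowance for attrition.

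Statistical analysis assigns a between-group t test, or a Mann-Whitney test for non-normal data, to each quantitative variable, with analysis of covariance for confounders. It gives no order of testing and no significance level.

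**The concern.** The error rate and power in the Sample size section describe one comparison, the one on weight. The outcome sections give seven measures equal standing. A report could therefore say that the primary outcome was met if, for example, weight showed no difference but hip circumference reached p = 0.04. Nothing in the text rules this out, and the 5% error rate does not cover such a claim.

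The list also mixes near-duplicates with distinct questions. Height is fixed in adults, so change in BMI is change in weight rescaled, and the two are almost the same measure. The food addiction score asks something different from the body measures and has no power calculation.

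**Working it through.** **Inputs from the protocol**
- Named primary outcomes: 7 (Objectives and hypothesis; Study outcomes).
- Sizing outcome: weight change, difference 2.3 kg, alpha 0.05, power 80%, 26 per group (Sample size).
- Allocation 1:1 (Randomization section).

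**Inputs assumed**
- Two-sided tests; the document does not state sidedness.
- 5% for each outcome; 0.05 is the only level given.
- No true effect on any outcome, with any one significant result counted as success.
- Correlations between the test statistics; the document gives none.

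**1. The plan's own figure.** No standard deviation is stated, so 26 per group cannot be reproduced directly. Solving n = 2(1.960 + 0.842)² SD² / 2.3² for n = 26 gives SD = 2.3 × √13 / 2.802 = 2.96 kg. The 80% power therefore belongs to weight, at alpha 0.05 and an SD of about that size. It says nothing about the other six outcomes.

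**2. Upper limits.** For k independent tests at 5%, the chance of at least one false positive is 1 − 0.95^k.
- k = 7: 1 − 0.95⁷ = 30.2%. This needs weight and BMI to be independent, which they cannot be.
- k = 6, with weight and BMI as one test: 1 − 0.95⁶ = 26.5%.

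**3. Equal correlation among all seven** (simulation, 1,000,000 draws of jointly normal statistics, any |z| > 1.96):

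| Common correlation | At least one false positive |
|---|---|
| 0.2 | 28.7% |
| 0.4 | 25.2% |
| 0.5 | 23.0% |
| 0.6 | 20.5% |
| 0.7 | 17.8% |
| 0.8 | 14.8% |
| 0.9 | 11.4% |

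**4. Structured correlations** (assumed), with weight–BMI at 0.99 throughout. The table shows the main entries. The remaining pairs were also varied, and waist-to-hip ratio was only weakly to moderately related to the rest.

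| Weight–fat mass | Weight–hip | Weight–muscle | Food addiction score with each other outcome | At least one false positive |
|---|---|---|---|---|
| 0.60 | 0.3 | 0.4 | 0.1 | 24.9% |
| 0.80 | 0.5 | 0.4 | 0.2 | 23.6% |
| 0.90 | 0.7 | 0.6 | 0.3 | 21.1% |
| 0.95 | 0.8 | 0.7 | 0.4 | 19.0% |

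These patterns give 19–25%.

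**5. What a correction would cost in power.** The weight calculation has 1.960 + 0.842 = 2.802 standard errors to work with.
- Bonferroni over seven: the threshold is 0.05/7 = 0.00714, critical value 2.690. Power for weight at 26 per group is Φ(2.802 − 2.690) = Φ(0.112), about 54%.
- Equal split over two outcomes: the threshold is 0.025, critical value 2.241. Power for weight is Φ(2.802 − 2.241) = Φ(0.560), about 71%.

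Keeping several primary outcomes and adding a simple correction would therefore break the stated 80% power.

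**The case against.** Several objections have force.

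- **The per-outcome 5% is not stated.** Alpha 0.05 appears only in the sample size calculation, and Statistical analysis gives no level. A reader might infer that the protocol prescribes seven separate 5% tests. It does not say so; the level is inferred because no other is offered. This stands.
- **A multiplicity rule may sit in an analysis plan that is not shown.** This also stands, so the absence of an adjustment is not the finding. Choosing the primary outcome, however, is a protocol decision. This protocol makes it explicitly in two sections, and the choice does not match its sample size section. A correction added later would also leave the stated power for weight untrue (step 5).
- **No rule says that one success is enough.** The expectation in Objectives and hypothesis refers to the indicators together. That is not an all-must-succeed rule, but neither does the document adopt an any-one rule. The inflated rate is conditional on reading it that way.
- **The size is uncertain.** A reader might quote 30% from seven tests. That needs an independence that weight and BMI cannot have. Nor is about 18%, the result at a common correlation of 0.7, a floor: stronger correlation gives less.
- **Sizing on one outcome is ordinary practice.** True, and no fault in itself. The difficulty is that the outcome sections give six others the same rank.

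**Conclusion.** The point holds in this form: the protocol fixes seven unranked primary outcomes, two of them nearly identical, and sizes the trial on one. With 5% per outcome and any single significant result taken as success, the false-positive chance for a primary claim is about 19–25% under the assumed correlation patterns. It is at most 26.5% with weight and BMI as one test, and about 11% if all seven correlate at 0.9, still more than twice 5%. The document does not support saying that it prescribes 5% tests on all seven, that it adopts an any-one-wins rule, or that the rate reaches 30%. The point affects what may be claimed from the results and can be corrected by wording, so it should be corrected.

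**What to change.** In Objectives and hypothesis and in Study outcomes, name change in body weight at week 8 as the single primary outcome, in line with Sample size. List the food addiction score, fat mass, muscle mass, BMI, hip circumference and waist-to-hip ratio as secondary outcomes, reported with 95% confidence intervals. The weight test then keeps its 5% error rate and its stated power basis.

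If a confirmatory claim on the food addiction score is wanted, which is reasonable because food addiction defines the population, prespecify how its error is controlled. Two options:
- Test it at 5% only if weight is significant. The downside is that there is no confirmatory test if weight is null, and Background notes that some earlier studies found no advantage of time-restricted feeding for body weight.
- Split alpha between weight and the food addiction score. The downside is less power for weight, about 71% with an equal split at 26 per group (step 5).

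Cost: Protocol amendments requires a formal amendment for changed objectives, agreed by the institute and approved by the ethics committee before it takes effect. The registry entry needs updating too. Trial status says the trial is still enrolling, so the change should be dated and made before outcome data are analysed. Six outcomes lose the primary label. No new participants, visits or measurements are needed.
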